## Abstract

**Background:**

Radiotherapy (RT) delivered in deep inspiration breath-hold (DIBH) is a simple technique, in which changes in patient anatomy can significantly reduce the irradiation of the organs at risk (OARs) surrounding the treatment target. DIBH is routinely used in the treatment of some adult patients to diminish the risk of late effects; however, no formalized studies have addressed the potential benefit of DIBH in children.

**Methods/Design:**

TEDDI is a multicenter, non-randomized, feasibility study. The study investigates the dosimetric benefit of RT delivered in DIBH compared to free breathing (FB) in pediatric patients. Also, the study aims to establish the compliance to DIBH and to determine the accuracy and reproducibility in a pediatric setting. Pediatric patients (aged 5–17 years) with a tumor in the mediastinum or upper abdomen with the possible need of RT will be included in the study. Written informed consent is obligatory. Prior to any treatment, patients will undergo a DIBH training session followed by a diagnostic PET/CT- or CT-staging scan in both DIBH and FB. If the patient proceeds to RT, a RT planning CT scan will be performed in both DIBH and FB and two separate treatment plans will be calculated. The superior treatment plan, i.e. equal target coverage and lowest overall dose to the OARs, will be chosen for treatment. Patient comfort will be assessed daily by questionnaires and by adherence to the respiratory management procedure.

**Discussion:**

RT in DIBH is expected to diminish irradiation of the OARs surrounding the treatment target and thereby reduce the risk of late effects in childhood cancer survivors.

**Trial registration:**

The Danish Ethical Committee (H-16035870, approved November 24th 2016, prospectively registered). The Danish Data Protection Agency (2012–58-0004, approved January 1st 2017, prospectively registered). Registered at clinicaltrials.gov (NCT03315546, October 20th  2017, retrospectively registered).

## Background

Long-term survival following childhood cancer is excellent, with 5-year overall survival rates exceeding 80% [1, 2]. It is, however, thoroughly documented that childhood cancer survivors suffer from a treatment-induced excess mortality and morbidity when compared to the general population or siblings [3–5].

Radiotherapy (RT) is known to induce late effects in childhood cancer survivors; primarily cardiovascular disease and second cancers [5–10]. Due to the long latency period, radiation-induced late effects are difficult to assess and quantify as they are often the consequence of treatment regimens now considered outdated. Nonetheless, the risk of radiation-induced late effects is known to be influenced by both the radiation dose and the volume of irradiated tissue [7, 11–13].

In modern RT, advanced imaging, highly conformal treatment planning and delivery techniques, as well as respiratory motion management systems have been introduced in the adult setting in order to reduce the radiation to healthy organs at risk (OARs) surrounding the treatment target. Deep inspiration breath-hold (DIBH) is a simple technique where the irradiation is delivered only while the patient holds his/her breath. A breath-hold in deep inspiration causes a change in patient anatomy (i.e. inflation of the lungs, rotation and elongation of the heart) and imaging artifacts from respiratory movement are diminished. The technique significantly reduces the radiation dose to the surrounding OARs, without compromising the delivered radiation dose to the treatment target, and with no detriment to other healthy organs [14–17]. The OAR dose reduction is estimated to reduce the risk of late effects [18]. Consequently, DIBH is widely used across the world for adult patients with left-sided breast cancer and mediastinal lymphoma.

However, the experience with DIBH in the pediatric setting is sparse [19, 20]. In general there has been a reluctance to implement new RT techniques in the pediatric setting as late effects data are not available with these new techniques. Regarding motion management systems an additional concern has been the skepticism about children’s compliance with breathing instructions.

With TEDDI we will introduce radio**t**h**e**rapy **d**elivery in **d**eep-**i**nspiration for pediatric patients within a multicenter setting through the NOPHO (Nordic Society of Pediatric Haematology and Oncology) network; accommodating the need for systematic research of RT delivery techniques in pediatric patients.

## Methods/Design

### Aims and hypothesis

TEDDI aims toEstimate the dosimetric benefit of RT using DIBH compared to free breathing (FB) in pediatric patients.

*Hypothesis 1: For more than 75% of patients, treatment in DIBH will be dosimetrically superior to treatment in FB.*

2)Establish the compliance of DIBH in pediatric patients.

*Hypothesis 2: Over 90% of pediatric patients from the age of five years will be able to perform stable, reproducible, and comfortable DIBHs (of 20 seconds) through their course of RT.*

3)Determine if DIBH is an accurate and reproducible strategy for pediatric patients.

*Hypothesis 3: The tumor position will be reproducible from day to day, as well as from DIBH to DIBH. Variations in tumor position will be less than 5 mm over the whole treatment course.*

### Patients

25 consecutive, pediatric cancer patients will be included.

Inclusion criteria:Age 5–17 years.Patients with a tumor in the mediastinum or upper abdomen with the possible need for RT according to current treatment guidelines, irrespective of cancer diagnosis.The ability to perform three sequential DIBHs of 20 s each during a training session.Written informed consent from parent(s) or legal guardian(s).

Exclusion criteriaAge < 5 years or > 17 years at time of diagnosis.The need for sedation during RT.CNS tumor or pelvic localization.Unable to understand DIBH coaching information directly or through interpretation.

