**Fig. 1 Fig1:**
[figure not shown]
A six year old healthy volunteer perform deep inspiration breath-hold using the Real-time Position Management system from Varian Medical Systems (Palo Alto, USA). The screen provides a visual feed-back and helps guide the volunteer’s  respiration. Notice how the immobilization device does not support the volunteer sufficiently; if the volunteer was to receive radiotherapy a custom made fixation device should be constructed

The patient is deemed compliant if he/she successfully completes three sequential DIBHs of 20 s each during the 20 min training session.

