### Safety

Procedures for patient safety and quality assurance during RT will be adhered to, irrespective of treatment in DIBH or FB. Patient compliance will be assessed through a questionnaire after each delivered RT fraction. Patients that initially or at any point during treatment cannot comply with the DIBH procedure will be treated in FB. A change from DIBH to FB must not cause a delay in the patient’s treatment course.

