### Data analysis

TEDDI is a non-randomized feasibility study and for this mainly descriptive statistics will be applied. The patient cohort will be described by demographic data, histological diagnosis, stage, age, and gender. For each patient, target volumes (GTV, CTV, and PTV) and OARs volumes of the two planning CT scans will be compared. Maximum and mean doses as well as the volumes exposed to 5/10/20/30 Gy will be compared. The Wilcoxon signed rank test for paired data will be used for statistical testing.

The dosimetric parameters are surrogate markers for the potential clinical benefit with DIBH compared to FB RT plans as an observed, significant reduction in treatment-induced late effects would require several decades of follow-up in a patient cohort consisting of several hundreds of patients. The expected clinical implications will, however, be estimated by applying normal tissue complication probability-models derived from clinical case-control and cohort studies.

Patient compliance is defined as patient comfort and DIBH reproducibility. Hence compliance will be assessed using both qualitative and quantitative measures. Patient comfort will be assessed through daily questionnaires based on a 5-point Likert scale. Tumor position will be used to evaluate the ability of patients to maintain the breath-hold during the whole course of treatment and to investigate the possibility that patients might get weaker and/or more tired and thus unable to perform a stable DIBH as the treatment course progresses. This will be done using the respiratory motion management system.

The accuracy of the treatment delivery will be evaluated based on daily imaging. If the target is not visible, the sternum (mediastinal tumors) or the diaphragm (abdominal tumors) will be used as a surrogate structure. If the target position appears reproducible within 5 mm, the patient will be deemed compliant. In addition to the daily online positioning at the treatment machine before each fraction, the reproducibility of the target position will be assessed retrospectively by a medical physicist on a weekly basis.

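### Hypothesis 2 claims a compliance rate for children from age five, but passing breath-hold training is an inclusion criterion, so the observed rate is conditional on passing and biased upward for that population

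*Protocol article*

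**What the plan says.** Aim 2 (Protocol article, Aims and hypothesis) is to "Establish the compliance of DIBH in pediatric patients". Its hypothesis reads "Over 90% of pediatric patients from the age of five years will be able to perform stable, reproducible, and comfortable DIBHs", each lasting 20 seconds, over the whole RT course. Neither sentence restricts the population to children who have passed a test.

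The inclusion criteria (Patients) require "The ability to perform three sequential DIBHs of 20 s each during a training session", and the exclusion criteria remove any child who is "Unable to understand DIBH coaching information directly or through interpretation". The Training session section, in the text under Figure 1, uses the same test as its definition of success: "The patient is deemed compliant if he/she successfully completes three sequential DIBHs of 20 s each during the 20 min training session".

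For the analysis, a different definition applies (Data analysis): "Patient compliance is defined as patient comfort and DIBH reproducibility". It is measured by daily questionnaires and by target position within 5 mm during treatment.

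Two places point to a different order of events. The abstract describes training after inclusion, and the Safety section says "Patients that initially or at any point during treatment cannot comply with the DIBH procedure will be treated in FB", where FB is free breathing.

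**The concern.** The population named in the hypothesis and the population admitted to the study are not the same. A child who does not manage three 20 s breath-holds in training fails an inclusion criterion and, as the Patients section is written, is not one of the 25. That child is also the one most likely to fail through RT, so the criterion removes likely failures from the denominator.

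The Background names doubt about whether children can follow breathing instructions as an obstacle to using these techniques. The Discussion cites an earlier study, with a spirometry-assisted method, that found only older children could comply. A compliance figure from this study would be read as an answer to that doubt for children from age five. From the cohort as defined, it answers a narrower question: how many children who passed training kept it up.

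**Working it through.** **The plan's own figure.** The only sample-size calculation (Sample size) concerns heart dose. Inputs: 25% of 4 Gy, so a difference of 1 Gy; SD 1.5 Gy (taken here as the SD of the paired difference); type 1 error 0.05 (taken as two-sided); 22 patients; power 0.85. The normal approximation gives n = (1.5 × (1.960 + 1.036) / 1)² = 20.2, so 21. The paired t-test with 22 patients has power 0.846. The stated figure reproduces. Compliance does not enter it, so this point leaves it untouched.

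**What the cohort estimates.** Let s be the training pass rate among otherwise eligible children who attempt it, c the through-RT compliance among passers, and d the compliance that training failures would have shown through RT. The rate in the stated population is

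R = s·c + (1 − s)·d,

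and the study observes c. The overstatement is c − R = (1 − s)(c − d), which is positive whenever some children fail (s < 1) and failures would comply less often than passers (d < c). If a training failure counts as non-compliance, in line with the Training session definition, then d = 0 and R = s·c.

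**Range.** The documents give no value for s; the pilot study in the Discussion is described without a figure. The values below are assumptions, with d = 0 and c = 0.95:

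| Pass rate s | R = s × 0.95 | Overstatement (percentage points) |
|---|---|---|
| 1.00 | 95.0% | 0 |
| 0.95 | 90.25% | 4.75 |
| 0.90 | 85.5% | 9.5 |
| 0.80 | 76.0% | 19.0 |
| 0.70 | 66.5% | 28.5 |

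At s = 0.90 even c = 1.00 gives exactly 90%, which is not over 90%.

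**In counts**, assuming all 25 included children receive RT:
- If all 25 comply, two excluded failures give 25/27 = 92.6% and three give 25/28 = 89.3%.
- If 24 of 25 comply (96%), one excluded failure gives 24/26 = 92.3% and two give 24/27 = 88.9%.

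**Chance of a misleading result.** Suppose R = 80%, so the hypothesis is false. An observed rate over 90% needs at least 23 of 25. With c = 0.80/s, the exact binomial probabilities are:

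| Screened out at training | c | P(at least 23 of 25) |
|---|---|---|
| 0% | 0.800 | 0.098 |
| 10% | 0.889 | 0.464 |
| 15% | 0.941 | 0.820 |
| 20% | 1.000 | 1.000 |

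**The case against.** The strongest reply is that the endpoint is compliance through the RT course and not the training test. A reader might infer that compliance in this cohort is 100% by construction. That holds only for the training-session definition. Under Hypothesis 2 and the Data analysis section, a child who passed training can still find the procedure uncomfortable, drift beyond 5 mm, or tire as treatment goes on. The rate among passers therefore carries real information. This part of the reply stands.

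Second, a reader might infer that failing children are certainly never included. The Safety wording about patients who cannot comply initially, and the order of events in the abstract, can be read as keeping them. This leaves some doubt, but neither place overrides an explicit inclusion criterion. If retention was intended, the criterion is wrong; if not, the hypothesis is too broad. One of them needs changing in either case.

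Third, a reader might infer that the bias is large or that Hypothesis 2 must fail. The documents do not support that: with 95% passing and 95% of passers complying, the combined rate of 90.25% still exceeds 90%.

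Fourth, this is a feasibility study with mainly descriptive statistics, no formal test of the 90% figure is specified, and a screening log is something an article may leave to the full protocol. This is fair, and it lowers the severity. The finding is not that a log is missing, however. The article states both the criterion and the hypothesis, and they refer to different populations.

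**Conclusion.** The point holds in a limited form. As written, the study estimates through-RT compliance given a passed training session, while Hypothesis 2 states it for pediatric patients from age five. For that population the observed rate is biased upward whenever any child fails training. The direction rests on one assumption: that training failures are counted as non-compliant, or would at least comply less often than passers. The size cannot be determined without a pass rate. On the assumed range it runs from nothing to 28.5 percentage points, and two or three unrecorded failures could move a result across the 90% line. Within the selected group the endpoint remains valid and useful. This should be fixed, but it does not undermine the study: the dosimetric comparison and its sample size are not affected.

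**What to change.** 1. Record every otherwise eligible, consented child who starts training, and treat training success as the first compliance outcome.
2. Report (a) the training pass rate among all who attempted, with an exact 95% CI, and (b) through-RT compliance among passers who start RT, with an exact 95% CI.
3. Judge Hypothesis 2 on the combined rate, in one of two ways fixed in advance:
   - The product of (a) and (b), with a delta-method or bootstrap interval. The product is not a single binomial proportion, so an exact binomial interval does not apply to it. It also assumes that passers who go on to RT are typical of passers.
   - The proportion compliant among children referred to RT, with training failures counted as non-compliant. This is a single proportion, but the log must also record RT referral for children who failed training.
4. State that passers who never receive RT contribute only to (a). Patients enter with only a possible need for RT, so some will have no through-RT outcome.
5. Reconcile the inclusion criterion with the abstract and the Safety section, so that it is clear whether children who fail training are in the study. How those children are treated is not part of this point.

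At minimum, restrict Hypothesis 2 to children who pass training and report how many attempted and failed.

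The cost is a small log and probably a lower reported compliance figure. If 25 is kept as the number who pass, more children must be recorded (25/0.9 = 27.8, about 28, at a 90% pass rate; 25/0.7 = 35.7, about 36, at 70%). Their training attempts are already needed to apply the criterion, so no procedure is added.

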### Patient information

Patient and parent(s) will receive written and oral information about the protocol and be accrued prior to start of any treatment (chemotherapy or surgery) at the Pediatric Department.

### Training session

The patient and parent(s) receive oral and written instruction on how to perform DIBHs. The information is adjusted to the individual patient’s age. At Rigshospitalet the Real-time Position Management (RPM) system from Varian Medical Systems (Palo Alto, USA) is used to perform and monitor DIBHs (during training, scanning, and treatment) [21]. The system consists of a small plastic marker box which is placed on the patient’s thoracic wall. The depth of inspiration is followed by an infra-red camera and expressed by the anterior-posterior displacement of the marker box. The patient is given visual feedback from a video screen which illustrates the level of inspiration; cf. Fig 1. Non-respiratory movement is detected through careful visual observation of the patient.

**Fig. 1 Fig1:**
[figure not shown]
A six year old healthy volunteer perform deep inspiration breath-hold using the Real-time Position Management system from Varian Medical Systems (Palo Alto, USA). The screen provides a visual feed-back and helps guide the volunteer’s  respiration. Notice how the immobilization device does not support the volunteer sufficiently; if the volunteer was to receive radiotherapy a custom made fixation device should be constructed

The patient is deemed compliant if he/she successfully completes three sequential DIBHs of 20 s each during the 20 min training session.

### Treatment planning

All diagnostic imaging during treatment and treatment planning will be performed according to national guidelines (as per cancer diagnosis). For optimal RT planning, the patient must be scanned upfront (pre-chemotherapy and/or pre-surgery) in the treatment position (i.e. in the supine position with arms raised over the head) in both DIBH and FB. This way the uncertainties in the image registration and fusion between the upfront imaging and imaging for treatment planning are minimized. Whenever a positron emission tomography (PET) scan is considered an integral part of the RT planning, a PET scan should be performed upfront as well [22]. The additional PET/computed tomography (CT) scan in DIBH can be conducted as a limited one-bed PET/CT scan over the mediastinal region, preferably in a joint session with the staging PET/CT scan. However, for institutions where this is not feasible, participation in TEDDI is still possible, and an upfront CT scan in both DIBH and FB will be sufficient.

For RT planning, a planning CT scan will be performed in DIBH as well as in FB for each patient.

Two RT plans will be made based on information from both pre- and post-chemotherapy DIBH and FB CT scans following international guidelines [23, 24]. On both scans the gross tumor volume (GTV), the clinical target volume (CTV), and the planning target volume (PTV) will be delineated. The PTV margin is left at the discretion of the treating institution and will be related to the specific positioning and image guidance strategies for each treatment site. All relevant OARs within the irradiated volume will be contoured (e.g. heart, female breasts, lungs, esophagus, thyroid, salivary glands, spinal cord, bone marrow, stomach, spleen, kidneys, and liver). The RT plan in DIBH and in FB will be calculated, both with similar planning objectives for the treatment target and OARs. All DIBH treatment plans will be designed to keep the number of breath-holds per fraction as low as reasonably achievable (including image guidance) for patient comfort.

### Treatment delivery

Patients will be treated in DIBH if the treatment plan in DIBH is superior to the treatment plan in FB with respect to the lowest overall dose to the OARs while maintaining acceptable target coverage. Coverage of the CTV and PTV will have the highest priority, as per ICRU83 guidelines [25]. The prioritizing of different OARs as well as the final choice of treatment plan will be at the discretion of the treating radiation oncologist.

To ensure the accuracy of the treatment delivery, image guided RT will be employed using daily volumetric imaging, planar kV imaging or surface imaging, depending on target location and institution.

Cf. Fig 2 for a display of estimated workflow during accrual and treatment planning.

**Fig. 2 Fig2:**
[figure not shown]
Chart of estimated workflow during accrual and treatment planning. *Abbreviations:* CT = computed tomography; DIBH = deep inspiration breath-hold; FB = free breathing; PET = positron emission tomography; RT = radiotherapy

### Follow-up

Enrollment in TEDDI will not affect the standard follow-up program of pediatric patients, which is diagnosis specific.

### Safety

Procedures for patient safety and quality assurance during RT will be adhered to, irrespective of treatment in DIBH or FB. Patient compliance will be assessed through a questionnaire after each delivered RT fraction. Patients that initially or at any point during treatment cannot comply with the DIBH procedure will be treated in FB. A change from DIBH to FB must not cause a delay in the patient’s treatment course.

### Ethical considerations

Patient consent files will be kept at the local institutions. All data (e.g. clinical report forms, imaging, and radiation treatment information) will be anonymized, and saved for a period of ten years. All data analysis will be performed in Copenhagen.

Patients participating in TEDDI will be exposed to an additional radiation of approximately 5 mSv originating from the additional staging PET/CT scan (or CT scan) in DIBH. This corresponds to approximately 1.5 years of exposure to the natural background irradiation. Patients who are referred to RT will receive additional approximately 10 mSv from the additional planning CT scan in DIBH. We expect the potential benefits of DIBH in terms of a reduced dose to the heart and lungs and possibly also other organs will markedly outweigh this additional risk.

